##### Measurements

Process evaluation

Similar to the process evaluation in the pilot study, attractiveness, feasibility, and enjoyment will be examined after each session of the finalized intergenerational movement program.

Effect evaluation

PA, cognitive functioning, psychosocial well-being, and quality of the family relationship will be measured in the grandchildren and grandparents to determine possible effects. A more detailed description is given in Outcome Measures Part in Section 2.2.3.

Outcome measures

According to the results of the accelerometers used in the pilot study, **physical activity** will be objectively measured in the grandchildren and grandparents using Axivity AX3 accelerometers or ActiGraph wGT3X-BT. These validated accelerometers in children and older adults [66,67,68] must be worn pre- (before the start of the sessions, at baseline), post- (right after the RCT ends, after 24 weeks), and for a third period at follow-up (after 36 weeks) for 7 consecutive days. This will be performed so as to examine changes in physical activity levels in the grandchildren and grandparents (due to the movement sessions and the encouragement to be more physically active at home) and to compare the effects of the intervention with the control group. The locations on the body will be on the wrist of the non-dominant hand for AX3 accelerometers [69,70] and on the right hip for the ActiGraph wGT3X-BT accelerometers [71]. The Bluetooth function of the ActiGraphs can give information about co-PA between the grandchildren and grandparents, but the feasibility of using this function in practice will be assessed. Additionally, a seven-day diary will be used to study the context of co-PA. For all activities, grandparents do (virtually) together with their grandchildren, they will write down which activities they performed, the start and end times of their activities, and their ratings of the perceived intensity of these activities. To monitor the intensity of PA of activities that the grandchildren and grandparents do together, the grandchildren and grandparents will also wear the accelerometers during certain sessions.

**The Cognitive functioning** of the grandchildren and grandparents will be objectively quantified pre- (before the start of the sessions, at baseline), post- (after 24 weeks), and at follow-up (after 36 weeks) by means of a validated neuropsychological test battery (i.e., CANTAB). The CANTAB is sensitive to changes in neuropsychological performance and allows the differentiation between different cognitive functions. The standardized and automated CANTAB can be used in children from the age of 4 and has been used and recommended in research in older adults [72,73]. Several specific cognitive functions, including 4 domains (i.e., ‘practice’, ‘attention’, ‘memory’, and ‘executive function and decision making’) will be objectively assessed using an iPad 10.2 with the validated CANTAB software (cambridgecognition.com, accecced on 12 January 2022).

**Psychosocial well-being** will be measured by several questionnaires that measure well-being indicators relevant to children and older adults. For children, the 23-item PedsQL (Pediatric Health-Related Quality of Life) scale will be used to obtain a reliable and valid global assessment of the children’s general quality of life and their specific emotional, social, and school functioning [54]. For older adults, general psychological well-being, depression, stress, anxiety, and social isolation will be measured. First, to capture a wide conception of older adults’ psychological well-being, including affective–emotional aspects, cognitive–evaluative dimensions, and psychological functioning, the Warwick–Edinburgh Mental Well-Being Scale (WEMWBS) will be used [51]. Symptoms of depression, (dis)stress, and anxiety will be measured using the Dutch version of the valid and reliable Four-Dimensional Symptom Questionnaire (4DSQ) [52]. Social isolation (defined as the way in which older adults perceive, experience, and evaluate isolation and lack of communication with others) will be measured using the valid and reliable Social and Emotional Loneliness Scale for Adults (SELSA) [53].

**Quality of the family relationship** will be measured in children with the Grandparent–grandchild Relationship Questionnaire using 3 sections (sociodemographic information, family, and participation in certain activities) and Rey and Ruiz’s Socialization Styles Questionnaire, which consists of 34 items on a 4-point Likert scale, and which evaluates democratic and authoritarian socialization styles [74]. In grandparents, this will be measured with a self-report questionnaire based on the previous investigations of Farneti and Battistelli. This 26-item questionnaire will assess the grandparents’ opinions concerning their relationships with their grandchildren using 3 subscales [75].

##### Data Analysis

Multilevel linear analysis in R will be used to estimate the between and within subject effects on PA, cognitive functioning, psychosocial well-being, and the quality of the familial relationship in grandchildren and grandparents. The mediating role of co-PA in the relationship between PA, cognitive functioning, psychosocial well-being, and the quality of the family relationship will be statistically checked in R using structural equation modelling (path analysis). Open-ended questions will be conducted using content analysis in SPSS (i.e., creating a code tree and looking for themes in the responses) [64].

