Health behaviour is, in general, influenced by the combination of three broad categories of determinants: capability, opportunity, and motivation (COM-B). In the co-creation sessions, the researchers will investigate why people show or do not show a specific behavior based on these three types of determinants (e.g., for the health behaviour of PA, are grandchildren and grandparents able to be physically active together; do they have opportunities to be physically active together; and are they motivated to be physically active together?). The sources of behaviour will be taken into account (physical, social, psychological, reflective and automatic), but other sources of behavior will also be considered (e.g., technological), which could result in an extended version of the BCW, including new determinants. 

Furthermore, the threats, barriers, and difficulties to setting the PA behavior will be investigated using the Theoretical Domains Framework (TDF). These TDFs are subcategories of the three broad categories. Examples of TDFs are given in Figure 3 [47]. 

The primary outcomes will be PA and cognitive functioning in both grandchildren and grandparents; the secondary outcomes will be psychosocial well-being and the quality of the family relationship between grandchildren and grandparents. We expect to see improved levels of PA, cognitive functioning, psychosocial well-being, and quality of the family relationship in the intervention group. Cognitive functioning will improve more in grandchildren and grandparents who participate in the cognitively enriched intergenerational movement program. 

Step 5: Intervention functions

The project researchers will consider the cases that emerged from Step 4 and will determine which intervention function is best suited to change the behaviour (i.e., a lack of PA). Intervention goals will also be drafted, which will then be presented to the grandchildren and grandparents in the co-creation sessions, where they can give their input and feedback. 

Step 6: Policy categories

In this step, policy categories will be identified. The policy categories will need to support the intervention functions in Step 5. It will be of great value that the sessions will be embedded in an organization afterwards so as to ensure sustainable implementation. Some examples of organizations and policy categories are Family Sport Flanders, senior and youth sports, and municipal sports.

Step 7: Behaviour change techniques

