To objectively measure PA in the grandchildren and grandparents, the Axivity AX3 accelerometers or the ActiGraph wGT3X-BT will be used. Half of the group doing the intergenerational movement program will wear the first accelerometer; the other half will wear the second one. During the cognitively enriched sessions, half of the group will also wear the first one; the others will wear the second one. The most feasible, practical, and useable of the accelerometers will be chosen to be used as a measure in the RCT. These accelerometers will be used in combination with a seven-day diary (pre- and post-follow-up) to subjectively measure PA, and they will be worn during certain sessions. More details about the measurement instruments are described below in Outcome Measures part of Section 2.2.3.

To objectively measure cognitive functioning in the grandchildren and grandparents, CANTAB tests will be used. The purpose will be to assess the feasibility, usability, and practicality of the test battery. The pilot study will be used to make a final selection of which cognitive tests to include in the RCT and decide on the ideal total duration of the cognitive testing procedure (e.g., +/− 40 min) based on practicality and discriminating power. More details are described in Outcome Measures part of Section 2.2.3.

To measure psychosocial well-being in the grandchildren and grandparents, several questionnaires will be administered. The preferred mode of delivery (online or paper-and-pencil questionnaires), the number of questionnaires, and the total duration of completing the questionnaires will be evaluated. Potential unclarities or difficulties when completing the questionnaires will be detected in order to improve this in the actual RCT. More details are described below in Outcome Measures part of Section 2.2.3.

Furthermore, participants will be asked for input and feedback on the measures and measurement instruments using a short questionnaire.

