#### 2.2.3. Randomized Controlled Trial (RCT)

The RCT will be conducted subsequent to the pilot study so as to measure the effects of the two different programs on the outcomes of PA, cognitive functioning, psychosocial well-being, and quality of the family relationship in the grandchildren and grandparents and to evaluate the process of the study. The RCT will consist of two intervention groups, Arm 1: Intergenerational PA and Arm 2: Cognitively enriched intergenerational PA, and one control group. Intervention Group 1 will receive the intergenerational movement program, Intervention Group 2 will receive the cognitively enriched intergenerational movement program, and the control group will receive no intervention. The pre- (before the start of the sessions), post- (after 24 weeks) and follow-up (after 36 weeks) outcome measures of PA, cognitive functioning, psychosocial well-being, and quality of the family relationship will be compared between Group 1 and the control group, between Group 2 and the control group, and between Groups 1 and 2. An overview of the RCT is shown in Figure 5.

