Arm 1 of the RCT will mainly focus on increasing co-PA (i.e., PA between grandchild and grandparent), while Arm 2 of the RCT will mainly focus on increasing cognitive functioning in both the grandchildren and grandparents via a *cognitive enrichment* of co-PA (i.e., cognitively enriched PA between grandchild and grandparent). The main goal and primary outcome of the intervention is to improve co-PA in grandchildren and grandparents (based on the WHO PA guidelines), and taking feasibility into account, we aim to reach a level where grandchildren are physically active together with their grandparents 2 times per week, for a minimum of 30 min of performing MVPA. The secondary goal is to improve total PA, cognitive functioning, psychosocial well-being, and quality of the family relationship in grandchildren and their grandparents, and it is expected that co-PA (over a period of 36 weeks) will act as a mediator in this relationship. It is hypothesized that Arm 1 (focusing on intergenerational PA) and Arm 2 of the RCT (focusing on intergenerational cognitively enriched PA) will lead to a greater improvement in PA, cognitive functioning, psychosocial well-being, and quality of the family relationship than that of the control group (no intervention). Furthermore, it is expected that the cognitive enrichment of the intergenerational movement program will lead to a greater improvement in cognitive functioning in Arm 2 of the RCT.

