## 4. Discussion of the Research Intention

This paper describes the study protocol of the GRANDPACT Project. The main aim of this project is to develop an effective, attractive, and feasible (cognitively enriched) intergenerational movement program for grandchildren and their grandparents to improve their co-PA and cognitive functioning (primary outcomes), psychosocial well-being, and the quality of the family relationship between the grandchildren and their grandparents (secondary outcomes).

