	**WHAT**		
3.	Materials: All the variables (physical activity, cognitive functioning, psychosocial well-being and quality of the family relationship) will be measured pre (at baseline, before the start of the sessions), post (after 24 weeks, right after the RCT ends), and for the third period at follow-up (after 36 weeks). To objectively measure physical activity, grandchildren and grandparents will have to wear Axivity AX3 accelerometers (wrist of the non-dominant hand) or ActiGraph wGT3X-BT (right hip). Grandparents and grandchildren also have to wear these accelerometers during certain sessions to measure the intensity of the activities that they do together. A seven-day diary will be used to study the context of co-PA. Cognitive functioning will be objectively quantified with the validated neuropsychological test battery (i.e., CANTAB) (cambridgecognition.com) using an iPad 10.2. Psychosocial well-being will be measured by several questionnaires that administer well-being indicators relevant for children and older adults. For children: PEDs-QL (Pediatric health-related Quality of Life scale). For older adults: Warwick-Edinburgh Mental Well-Being Scale (WEMWBS), Four-Dimensional Symptom Questionnaire (4DSQ), Social and Emotional Loneliness scale for Adults (SELSA). Quality of the family relationship will be measured in children with the Grandparent-grandchild Relationship Questionnaire. For older adults, this will be measured with a self-report questionnaire, based on previous investigations of Farneti & Battistelli.	pp. 16–17	_____________

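### The primary outcome is stated in three conflicting ways, and co-PA, primary in two of them, has no between-arm test in the RCT

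*Protocol article*

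**What the plan says.** **Primary outcome, three statements.**
- Section 2.1.1, Step 4 of the Behaviour Change Wheel: "The primary outcomes will be PA and cognitive functioning in both grandchildren and grandparents".
- Section 3, Research Intention: "The main goal and primary outcome of the intervention is to improve co-PA in grandchildren and grandparents". The same paragraph places total PA and cognition among the secondary goals and sets a co-PA target of two joint occasions a week, each with at least 30 minutes of MVPA.
- Section 4, opening paragraph: the aim is to "improve their co-PA and cognitive functioning (primary outcomes").

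The Abstract, the last paragraph of the introductory text in Section 3, and TIDieR item 1 also say that the RCT will measure or evaluate effects on co-PA. Section 4.3 makes the implementation step depend on the RCT showing improvement in co-PA and cognition first.

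**What the RCT text specifies.**
- Section 2.2.3, opening paragraph: "outcome measures of PA, cognitive functioning, psychosocial well-being, and quality of the family relationship will be compared between Group 1 and the control group", and likewise for the other two pairs of arms.
- Participants and Sample Size: effect size 0.15, alpha 0.05, 80% power, 3 groups and 3 measurements, for those four outcomes; around 45 dyads (90 people), raised to 54 dyads (108 people) for attrition.
- Measurements, effect evaluation: the same four outcomes.
- The analysis paragraph that closes Section 2.2.3 reads: "Multilevel linear analysis in R will be used to estimate the between and within subject effects on PA, cognitive functioning, psychosocial well-being". Family relationship is the fourth and last outcome named there. Co-PA follows as a mediator in a path analysis.
- Appendix A, TIDieR item 3: "All the variables (physical activity, cognitive functioning, psychosocial well-being and quality of the family relationship) will be measured pre", post and at follow-up.

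**Co-PA data that are planned.** Under Outcome measures, "a seven-day diary will be used to study the context of co-PA"; grandparents log the activity, its start and end times and its perceived intensity. ActiGraph Bluetooth may add information if feasible, and accelerometers are worn in certain sessions.

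**The concern.** A trial's primary claim needs a defined variable and a comparison between arms. Here the outcome that Section 3 calls the main goal has neither, while an outcome that Section 3 calls secondary has both.

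The gap cannot be closed by reading PA as co-PA. A child or grandparent can become more active without the other, which raises total PA and leaves co-PA unchanged. A pair can also swap separate activity for joint activity, which raises co-PA and leaves total PA unchanged. A test on total PA therefore neither supports nor refutes a claim about co-PA.

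With three versions of the primary outcome and no fixed co-PA variable, the choice of which result is primary, and how co-PA is computed, could be made after the data are seen. A statistical analysis plan faithful to this article would not resolve this, because the article itself lists which outcomes are compared, powered and modelled.

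**Working it through.** **1. Passages side by side**

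| Place in the article | PA | Cognition | Co-PA |
|---|---|---|---|
| Section 2.1.1, Step 4 | primary | primary | not listed |
| Section 3 | secondary | secondary | primary |
| Section 4 | not listed | primary | primary |
| 2.2.3, arm comparisons | yes | yes | no |
| 2.2.3, power statement | yes | yes | no |
| 2.2.3, effect evaluation | yes | yes | no |
| 2.2.3, multilevel analysis | yes | yes | no (mediator only) |
| TIDieR item 3, list of variables | yes | yes | no |

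Under Step 4, both primary outcomes are compared and modelled. Under Section 4, one of two is. Under Section 3, none is. The between-arm hypotheses in Section 3 also leave co-PA out.

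**2. What the stated sample size was derived for**

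Inputs from the article: effect size 0.15, alpha 0.05, k = 3 groups, m = 3 measurements, 80% power, N = 90 people. Assumptions, because the article does not give them: the effect size is Cohen's f, the correlation between repeated measures is rho = 0.5, sphericity holds, and the test is the group-by-time interaction.

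Noncentrality: lambda = f² × N × m / (1 − rho). Degrees of freedom: df1 = (k − 1)(m − 1), df2 = (N − k)(m − 1).

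- N = 90: lambda = 0.0225 × 90 × 3 / 0.5 = 12.15; df = 4 and 174; power 79.6%. The smallest N reaching 80% is 91.

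This reproduces the article's figure of around 90. It does so with the 90 people counted as independent units. The other standard tests in this family do not give 90 at rho = 0.5: the within-subject effect needs 73 and the between-group effect 289.

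**3. The same calculation with one co-PA value per dyad**

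The article gives no effect size, SD or correlation for co-PA, so f = 0.15 is carried over for illustration only.

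- 45 dyads, rho = 0.5: lambda = 0.0225 × 45 × 3 / 0.5 = 6.075; df = 4 and 84; power 45%.
- 54 dyads, rho = 0.5: lambda = 0.0225 × 54 × 3 / 0.5 = 7.29; df = 4 and 102; power 54%.

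| Assumed rho | Power, 45 dyads | Power, 54 dyads | Dyads for 80% (before attrition) | f detectable with 80% power, 45 dyads |
|---|---|---|---|---|
| 0.3 | 33% | 39% | 127 | 0.26 |
| 0.5 | 45% | 54% | 91 | 0.22 |
| 0.7 | 69% | 79% | 56 | 0.17 |

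The last column solves the same power formula for f at N = 45.

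**4. Whether a co-PA variable can be built from planned data**

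The diary records start and end times of joint activities. Both members wear an accelerometer for seven days at baseline, 24 weeks and 36 weeks. Matching the two gives the intensity recorded by each member during each logged joint episode, with either the AX3 or the ActiGraph. Accelerometry during sessions cannot feed a between-arm comparison, because the control group has no sessions.

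**The case against.** **The premise is not settled.** Step 4 names PA and cognition, and both are tested. This stands, and it limits the conclusion: the statement that the trial never tests its main question is fully true only under Section 3. It does not remove the problem, because three versions cannot all hold.

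**Loose wording.** The Abstract and Section 3 put co-PA in the slot where Section 2.2.3 puts PA, and co-PA measurement sits under the physical activity heading. Interchangeable terms may be part of the explanation. But Section 3 ranks co-PA above total PA, and TIDieR item 1 lists the two separately, so the terms cannot be treated as one.

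**Co-PA is measured.** Correct: the diary, conditional Bluetooth and in-session accelerometry are planned. What is absent is a co-PA outcome and its comparison between arms, not data.

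**The path analysis could yield an arm effect on co-PA.** It could, but as described it concerns relations among the outcomes and names no such effect.

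**Detail for a statistical analysis plan.** The exact derivation may be left there. Which outcome is primary, and whether it is compared between arms, may not, since the article fixes those points and contradicts itself.

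**Stronger readings that a reader might infer.** One is that Bluetooth is the only objective route to co-PA, so that choosing the AX3 would leave an unblinded diary alone. The pilot section does choose the device on practical grounds: "The most feasible, practical, and useable of the accelerometers will be chosen to be used as a measure in the RCT". Logged times can be matched to either device, however, so this does not follow. Another is that the joint-activity target, set against the children's weekly guideline total, measures how far total PA dilutes co-PA. It does not: the guideline is not observed activity, the target is a minimum, and grandparents have a different guideline.

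**Conclusion.** The concern holds as an internal contradiction. The article gives three incompatible primary outcomes. In two of them co-PA is primary, yet all five places that specify the RCT's comparisons, power, measured outcomes and model leave it out. As written, no between-arm test addresses co-PA, and total PA cannot stand in for it. This part rests on the text alone and needs no assumption.

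The power result is weaker and should be reported as such. It is certain that the 80% is stated for four outcomes that exclude co-PA. That power for a dyad-level outcome would be lower rests on carrying over f = 0.15; with rho from 0.3 to 0.7, power is 33% to 69% at 45 dyads and 39% to 79% at 54. Co-PA is the behaviour that the programme targets, so its effect could be larger than 0.15. At 45 dyads and rho = 0.5, an f of about 0.22 would restore 80%. The documents do not support a claim that the trial is underpowered for co-PA, only that its power for co-PA is unknown and may be below 80%.

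**What to change.** 1. State one primary outcome, in the same words, in Section 2.1.1 (Step 4), Section 3 and Section 4.
2. If it includes co-PA, define a dyad-level variable. One example is minutes per week in which both members record accelerometer MVPA during joint episodes timed by the diary. Have all three arms complete the diary in each accelerometer week and derive the variable identically in each.
3. Add co-PA to the arm comparisons, sample-size paragraph, effect evaluation and Data Analysis in Section 2.2.3 and to TIDieR item 3, with a between-arm comparison at 24 weeks from the multilevel model. The mediation analysis can remain as a secondary analysis.
4. Acknowledge among the limitations that the diary identifying joint episodes is self-report by unblinded grandparents, compared with a no-intervention control.
5. Reword the sample-size paragraph so that 80% power is not claimed for co-PA. Either give a calculation with the dyad as the unit and a justified effect size and correlation, or state the power expected at 45 to 54 dyads.

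No change to the basis for choosing the accelerometer is needed.

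**Cost.** Items 1 to 4 need wording and one derivation step on data already planned; the article says that the RCT is still to be registered, so the registration can carry the reconciled outcome. Item 5 may cost more: it could show that more dyads are needed, or that a less precise co-PA estimate must be accepted.
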